## Abstract

The website Sexe Joves is a website on sexuality of the Department of Health of the Government of Catalonia (Spain). This study aims to understand the experiences and opinions of people aged 14 to 25 regarding this website, taking into account sex, gender identity, sexual orientation, socioeconomic status and location within Catalonia (urban, semiurban and rural areas). With the objective of improving the website and adpating the resources allocated to it, this study evaluates whether this population is familiar with it and uses it, as well as the website’s usability and accessibility (digital equity), usefulness and the relevance of its content. A parallel convergent triangulation design is used: a qualitative study using a social constructivist perspective, and an observational, descriptive and cross-sectional quantitative study. We conduct a discourse analysis of participants and use an “ad hoc” questionnaire to collect quantitative data. A descriptive analysis of all variables is carried out. Affective-sexual education aimed at young people must stem from their participation and the whole range of sexual and gender diversity in order to reach the entire population equally. This analysis will contribute to the design of new strategies for the wesbite Sexe Joves, a public health resource, in order to improve affective-sexual education for young people.

## 1. Introduction

Health professionals have implemented sex education for adolescents for decades. Oftentimes, such education has not been based on a holistic model of health but focused solely on preventing sexually transmitted infections (STIs) and unplanned pregnancies. This model replicates heteronormative sexuality and drives young people to use mainstream pornography [1].

Affective-sexual education for young people pivots on a positive sexuality, which is understood as something to be enjoyed, not centred around fear, and removed from the coitocentric, biomedical, heteropatriarchal and binary model. This type of sexuality is based on self-esteem and self-care, as well as respect and empathy [1]. It should be a dynamic and holistic process that includes sharing information, enabling communication, and the transformation of attitudes, beliefs and values. Broadly, the objectives are young people taking responsibility for their own actions and behaviours, equality between the different sexes and gender identities, acceptance, intolerance of violence, and empathy. In this way, affective-sexual education should represent a new paradigm that consists of working with adolescents and young adults on affection, emotions, interpersonal relationships and pleasure [1,2] so that they can fully enjoy a healthy sexuality that respects themselves and others, from a comprehensive biological, psychological and social perspective.

Global data support the need for this type of research. Violence against women by their intimate partners and others is currently considered a major public health problem [3]. In Spain, the number of complaints against minors due to gender violence tripled between 2008 and 2017 [4]. Unfortunately, sexist attitudes within couples persist in younger generations. An astonishing 27% of young people in Spain believe that gender violence is normal within couples, and over 80% reported being aware of acts of abuse in couples in their age range [4]. Data on sexual assault not perpetrated by intimate partners from 15 years of age show that between 0.3% and 12% of women have suffered some act of sexual violence [5]. Furthermore, studies have shown that the highest risk of sexual violence occurs during adolescence and young adulthood [6].

Statistics show an upward trend in the diagnosis of STIs, a consequence of risky sexual practices without the use of barrier methods [7]. Worryingly, it appears that only a minority of young people in Europe have adequate information on sexual issues [8]. Experts emphasize the need to improve sexual education, start education on gender roles from an early age and address the harmful effects of the romantic love paradigm [9]. They also underscore that we cannot just treat STIs, but need to use a personalized psychosocial approach for each case [10,11].

In agreement with the Istanbul Convention [12], discussions on gender equality should be urgently implemented at all levels of education. Affective-sexual education is an essential element of the 2030 Agenda for Sustainable Development and its 17 Sustainable Development Goals (SDGs) approved by world leaders in 2015 [13].

In 2016, the Guttmacher Institute and The Lancet created a commission on Sexual and Reproductive Health and Rights (SRHR). They concluded that the 17 SDGs are insufficient for a broad implementation of SRHRs [14]. In their report, they denounce inequities between and within countries where a sector of the population cannot access adequate resources. The commission underscored the need for a comprehensive look at sexual and reproductive health, with special emphasis on adolescent sexuality, gender-based violence, abortion and the diversity of sexual orientations and gender identities [15]. Additionally, the socioeconomic perspective indicates that women in the lower socioeconomic strata use less effective contraception and are at higher risk of unplanned pregnancies [16]. Studies indicate that inequalities in sexual and reproductive health occur both in migrants and native residents of disadvantaged urban neighbourhoods [17].

In order to improve these indicators, guidelines and programs on sexual health for young people should be re-evaluated and include the thoughts, experiences and opinions of the target population. The result should be an affective-sexual education that is truly effective.

### 1.1. Background

Affective-sexual health education for young people in Catalonia is provided by the public universal primary care system, specifically from the Reproductive and Sexual Healthcare units (ASSIR, Atenció a la Salut Sexual i Reproductiva) [2,18]. This education can be imparted during individual consultations, youth community events (for instance, the Youth Afternoon), and also from institutional websites [19].

The website Sexe Joves (WSJ) on sexuality is a reference for health professionals in Catalonia (www.sexejoves.gencat.cat). The project started in 2003 and was fully operative in 2006. It was led by midwives from the outset, with support from the government of Catalonia and the Catalan Institute of Health (Institut Català de la Salut (ICS)). A multidisciplinary team of 65 professionals from various institutions related to sexuality and youth participated in the creation process. This group prepared a document with content for the website, which was validated by a total of 153 young people from secondary schools from across Catalonia [19]. The main aims are twofold: (1) to help young people enjoy a healthy and responsible sexuality; and (2) to prevent unplanned pregnancies and STIs. The website offers information on affection, self-esteem, knowledge about one’s body, abuse, harassment, sexual assault, sex and drugs, and virtual sex. It also includes a virtual consultation room (email and chats), where a team of midwives provides individualized care, and links to health centres that offer face-to-face and/or telephone consultations.

The website is designed for 14- to 25-year-olds and is accessible to people with hearing, eye and motor impairment. It is also used as a consultation tool for adults, health professionals, educators and others. The advice takes into account sex, sexual orientation and gender identity [20]. The WSJ has a multidisciplinary editorial committee, which consists of nine midwives, two psychologists, a gynaecologist, an administrator and two senior public health technicians from the Catalan government, and is coordinated by the midwife who launched the project. The committee is responsible for the day-to-day running of the website, updating its content and analysing indicators such as number of visits, telematic consultations and most consulted topics [20].

Although the website has been operative for 16 years, it was only evaluated in 2012, as part of a doctoral dissertation [19]. Through a quantitative study with a descriptive design that analysed sevaral variables from the website, as well as the user satisfaction of young people, it was concluded that at that time, the WSJ had a high usability (in a website or computer program refers to ease of use, taking into account readability of texts, speed of download, manageability and capacity to meet the needs of the user [21]) rate. In the second phase of the same doctoral dissertation, an analysis was conducted to evaluate the quality of responses from the midwives with a validated questionnaire. In the third phase, a quasi-experimental study was performed, pre- and post-training, of the midwives in charge of responding to the website’s virtual consultation. The dissertation conluded that the quality of responses to emails was high and that up-to-date training of professionals who answer these emails would be sufficient to reduce inadequate responses [19]. The editorial committee has now commissioned the research team of this project to undertake an in-depth evaluation of the website centred around the voice of the youth of Catalonia.

The Sexunzipped website for the UK population over the age of 16 is one of several affective-sexual education websites that have been created and/or evaluated through research projects [22,23]. Bailey’s group has used this website for quantitative and qualitative research projects. In 2012, they conducted a qualitative study with people aged 16 to 22 that included 21 focus groups and 6 in-depth interviews to understand preferences regarding the content and format of Sexunzipped [24]. They later published a randomized trial describing the quantitative evaluation of the website and its content [25]. In 2013, they presented the results of a mixed-methodology study that used in-depth interviews and analysis of emails/chats and questionnaires to explore the views of young people on STI screening using Sexunzipped and mail-in samples [26]. In December 2013, Bailey’s group used Sexunzipped to conduct an online randomized controlled trial with people aged 16 to 20 living in the United Kingdom to assess the feasibility of the various dimensions of the design of online clinical trials [27]. In the last five years, Bailey’s group has evaluated interventions using mobile text messages, tablets in the waiting rooms of sexual health services, and social networks [28,29].

Templeton et al. also investigated the promotion of sexual health in young people, in their case using a qualitative methodology with participatory interventions and prison populations. In their systematic review, they conclude that qualitative and participatory methodologies that incorporate what young people really want are essential for effective change [30].

The literature review supports the use of mixed methods to explore the point of view of young people on the WSJ. The results of this study will contribute essential data to determine new strategies for the sustainability and relevance of the WSJ. It also aims to provide a holistic perspective of affective-sexual health that includes (1) sexual and gender diversity and (2) socioeconomic factors. The results might also provide advice for professionals of primary healthcare, school health and community nursing.

### 1.2. Aims

#### 1.2.1. General Objective of the Project

To evaluate the WSJ as a source of affective-sexual health information, education and communication for young people.

#### 1.2.2. Specific Objectives of the Project

To outline a new participatory model of affective-sexual education for adolescents and young adults led by midwives and/or nurses that incorporates the gender perspective and sexual and socioeconomic diversity (we will use the Territorial Socio-Economic Index (IST) to determine socioeconomic conditions. This is a synthetic index that summarizes in a single value several socioeconomic characteristics of the population by small areas. The index includes data on employment, educational level, immigration and income of all people living in each territorial unit, based on six sectoral indicators [31]) and that can be used by health professionals working with young people.To provide a new framework for the WSJ that is competitive and effective with regard to the affective-sexual education of young people.To involve the target population in the creation of this intervention for their emotional and sexual wellbeing.

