#### 1.2.4. Quantitative Part of the Study

General objective: To understand how the youth population of Catalonia evaluates the WSJ.

Specific objectives:To determine what content of the WSJ receives the best rating by young people.To identify whether assessment of content and usability of the WSJ varies according to the following factors: age, sex, gender identity, sexual orientation, culture of origin, socioeconomic status, area of residence (urban, semiurban or rural) and motivation for consulting the website (of their own accord or suggested by a professional).To identify whether assessment of content of the WSJ is different in young people that had previously used it.To assess if having previously consulted the ASSIR unit is associated with a different assessment of the WSJ content.To determine if the target population knows about the WSJ, and what percentage use it and consider it useful.To evaluate if socioeconomic conditions determine the use of paper vs. digital questionnaires.To determine if young people in Catalonia visit other affective-sex education websites, and which are the most popular.To determine if young people in Catalonia follow any influencers for affective-sexual education, and which influencers are the most popular.To determine the percentage of young people in Catalonia that visit pornography websites.

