#### 2.4.2. Quantitative Part of the Study

In the context of COVID-19, we have both an online (Microsoft Forms) and paper version of the questionnaire (Teleform). The online questionnaire can be accessed via direct link or QR code. The questionnaire consists of 24 closed questions and 2 open-ended questions. The questionaire is available in Supplementary Material (Figure S1).

At the education centres: The recruiting researchers will communicate with these centres to disseminate the questionnaire among students. The centre directors will decide if their centre will use the online or paper questionnaire.At the ASSIR units: a wide network of professionals are also researchers that will recruit for the study. The study will be disseminated through posters in the waiting rooms and at the counter of each ASSIR unit. These posters will contain the study instructions and the QR code for the questionnaire so that young people can quickly download it to their mobile phone and answer it. There will also be a paper version of the questionnaire for people unable to access it digitally. Digital users of the ASSIR will be sent the link to the questionnaire with information to encourage them to answer on the same platform they used for the consultation (email, WhatsApp^®^, e-consultation).WSJ users who make email inquiries will automatically receive an email with the direct link to the questionnaire, encouraging them to participate after explaining that this is a study to evaluate the website. The study will be also advertised on the WSJ homepage through images with a direct link to the questionnaire.

Whatever the origin of the participant, the variables that will be evaluated for all the participants in the sample through the questionaire are the following:

Sociodemographic variables: age, sex, gender identity, sexual orientation, country/culture of origin, years of residence in Spain, postal code, socioeconomic condition of the postal code according to the Territorial Socio-Economic Index, city/rural/semirural residence, current job, ongoing studies, type of access to the questionnaire (electronic or paper).

Variables related to the WSJ: prior knowledge of the WSJ, use of the WSJ, usability of the WSJ, usefulness of the WSJ, rating of affective-sexual education content.

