#### 2.6.2. Quantitative Part of the Study

We will perform a descriptive analysis of all variables, using frequencies and percentages for categorical variables and mean and standard deviation for age and years living in Spain. Familiarity with the website will be summarized with a percentage and confidence interval. The bivariant analysis will be performed using Pearson’s chi-squared test or Fisher’s exact test to find associations between the assessment of WSJ and the sociodemographic variables. If the bivariant analysis shows any associations, a multivariant analysis using a regression model with assessment of WSJ as the outcome variable is planned. The anlaysis will be performed disaggregating by gender. Significance level is set at 5%. SPSS statistical package for Windows, version 25.0, will be used for all analyses.

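### The area socioeconomic index includes immigration, so one-factor-at-a-time tests cannot separate it from respondents' culture of origin; the two should always be estimated jointly

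*Protocol article*

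**What the plan says.** Section 1.2.2 of the protocol article adopts the Territorial Socio-Economic Index: "This is a synthetic index that summarizes in a single value several socioeconomic characteristics of the population by small areas". Its inputs are named, immigration among them ("The index includes data on employment, educational level, immigration and income of all people living in each territorial unit"), and it is "based on six sectoral indicators". The weight of immigration is not given.

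Section 1.2.4 asks whether ratings of content and usability vary by "age, sex, gender identity, sexual orientation, culture of origin, socioeconomic status, area of residence (urban, semiurban or rural" and by reason for visiting. Origin and socioeconomic status are thus two factors in one objective. A later objective asks whether socioeconomic conditions determine paper or digital completion.

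Section 2.4.2 records origin for each respondent but attaches socioeconomic status through the address: "socioeconomic condition of the postal code according to the Territorial Socio-Economic Index". Job and studies are also recorded individually.

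Section 2.6.2 begins with chi-squared or Fisher tests of the website assessment against each sociodemographic variable. A joint model is conditional: "If the bivariant analysis shows any associations, a multivariant analysis using a regression model".

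**The concern.** An area with more immigrants scores differently on the index by construction, and its respondents are more often of other origin. A one-factor test of the index then carries part of any origin effect, and a one-factor test of origin carries part of any socioeconomic effect. The Introduction itself distinguishes the groups ("inequalities in sexual and reproductive health occur both in migrants and native residents of disadvantaged urban neighbourhoods"), and the Conclusions make the socioeconomic perspective one of two axes of the evaluation.

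What is at stake is attribution. A gap related to origin points to cultural adaptation of the website; a gap related to deprivation points to digital or economic access. If the two are mixed, the wrong remedy may be chosen, or a real socioeconomic gap may go unseen.

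**Working it through.** **1. The plan's own figure.** Section 2.3.2 gives 388 per group for 0.5 against 0.4, two-sided alpha 0.05, power 80%. With pooled variance, n = [1.96·√(2·0.45·0.55) + 0.8416·√(0.25 + 0.24)]² / 0.1² = (1.379 + 0.589)² / 0.01 ≈ 387.3, so 388 per group and 776 in total. It reproduces. It concerns the reason for visiting and does not depend on the present point.

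**2. How much of the overlap is composition (assumption: six equally weighted, standardised indicators, one of them immigration, common correlation r).**
- Correlation of the full index with immigration = (1 + 5r)/√(6 + 30r). For r = 0 this is 1/√6 = 0.41; for r = 0.5 it is 3.5/√21 = 0.76.
- With immigration removed it is 5r/√(5 + 20r). For r = 0 this is 0; for r = 0.5 it is 2.5/√15 = 0.65.

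At r = 0.5, 0.65/0.76 ≈ 85% of the correlation remains without immigration in the index. Most of the overlap there is the ordinary association of immigration with deprivation.

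**3. Leakage into the gradient.** Spurious gradient = difference in migrant share between outer index tertiles × origin gap. A simulation with about 22% migrants and 400 areas gave shares of 0.29 against 0.17 (r = 0) and 0.36 against 0.12 (r = 0.5). For a 20-point gap that is 0.12 × 20 = 2.4 points and 0.24 × 20 = 4.8 points.

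**4. False-positive rate, no true socioeconomic effect.** Simulation with n = 776, 150 areas, 1,000 runs per setting and a three-tertile chi-squared test, against logistic regression with origin included. The rating is 0.5 in natives and 0.4 or 0.3 in others. Here w is the assumed weight of immigration against a composite of the other indicators, and ρ is the correlation between the two.

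| Origin gap | w | ρ | Correlation of origin with index | Spurious gradient (points) | One-factor rejection | With origin in model |
|---|---|---|---|---|---|---|
| 10 | 0 | 0 | 0.00 | 0.3 | 6.7% | 6.8% |
| 10 | 0 | 0.5 | −0.14 | 1.3 | 4.7% | 4.8% |
| 10 | 1/6 | 0 | −0.06 | 0.3 | 4.9% | 4.8% |
| 10 | 1/6 | 0.5 | −0.19 | 1.4 | 6.8% | 6.0% |
| 10 | 1/3 | 0 | −0.13 | 0.9 | 4.0% | 3.5% |
| 10 | 1/3 | 0.5 | −0.22 | 2.0 | 6.6% | 4.6% |
| 20 | 0 | 0 | 0.00 | 0.1 | 4.6% | 4.2% |
| 20 | 0 | 0.5 | −0.15 | 2.8 | 8.2% | 4.5% |
| 20 | 1/6 | 0 | −0.06 | 1.0 | 4.8% | 4.2% |
| 20 | 1/6 | 0.5 | −0.18 | 3.4 | 8.8% | 5.1% |
| 20 | 1/3 | 0 | −0.13 | 2.3 | 7.9% | 5.4% |
| 20 | 1/3 | 0.5 | −0.22 | 3.8 | 12.2% | 5.5% |

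The simulation standard error at 5% is √(0.05·0.95/1000) = 0.7 points, so the 10-point rows are about nominal. The 6.7% with no overlap at all is noise.

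The set-up in step 3, which compares the outer tertiles only (1,500 runs, 20-point gap), gave 8.7% (r = 0) and 20.5% (r = 0.5). A further set-up with 400 areas, w = 1/6, a 20-point gap and weak or strong clustering of origin by area gave 4.6% to 17.8%, and 4.1% to 5.0% with origin in the model. The range for a 20-point gap is therefore about 5% to 20%.

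**5. Masking.** In that last set-up, with a real socioeconomic gradient of about 10 points, the one-factor test had 51% to 59% power when there was no origin effect. With an opposing 20-point origin effect it had 21% to 40%, and with origin in the model 53% to 62%.

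**The case against.** Four points on the other side carry weight.

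- **The regression is planned.** A spurious index gradient is itself a bivariate association and so triggers the model; the inflated rates describe the first step, not the whole sequence. A reader might infer that when the two effects cancel, the regression is never run. The text does not support that: the trigger is any association. Even if all seven respondent characteristics listed were truly null and independent, 5% tests would trigger it with probability 1 − 0.95⁷ ≈ 30%, and a large origin effect would nearly always do so through origin itself. What stands against the plan is that joint estimation remains conditional on the one-factor results, and that the index could be left out of the model because its own one-factor test was masked.
- **Different levels.** The index describes all residents of an area; origin belongs to the respondent. They are not one variable counted twice. This is correct, and it is why both can be fitted together.
- **Ordinary confounding.** Any deprivation index would correlate with origin. Step 2 and the w = 0 rows confirm it. Removing immigration from the index is therefore not the main remedy.
- **Scale and context.** A 20-point gap is twice the only difference in the protocol. Participants must be able to express themselves in Catalan or Spanish (section 2.3), which limits any language explanation. The covariate list may properly sit in a fuller plan, so its absence from the article is not held against it here.

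**Conclusion.** The point holds in a limited form. The overlap is in the text: the index contains immigration, origin is a separate factor in the same objective, and the first-line tests cannot separate them. An origin difference can appear as a socioeconomic gradient, and an opposing origin effect can mask a real one.

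A reader might infer that part of any origin difference will be reported as a socioeconomic gradient. The documents do not support that certainty, since they give neither the immigration weight, nor the distribution of origin, nor its clustering by area. Every rate above is conditional on assumed values for these. For a 10-point gap the error rate is about nominal (4% to 7%); for a 20-point gap it runs from about 5% to 20%, the top needing correlated indicators and strong clustering. Adjustment for origin brings it back to 3.5% to 6.8%. The masking result rests on a single set-up.

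This is a matter of analysis and interpretation. It does not touch the sample size.

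**What to change.** In section 2.6.2, state that the index association is estimated in a model that always includes individual country or culture of origin, whatever the bivariate tests show. Do this for the website assessment and for paper against digital completion. Base any conclusion about socioeconomic status or origin on that joint model, keep the one-factor tables as description, and describe the index as an area-level measure.

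If the component indicators are available, an index without immigration may be added as a sensitivity analysis only. Nothing in the article shows that the team holds more than the single index value.

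The cost is a little extra analysis on data already collected and slightly wider intervals. At the largest correlation in the table (0.22) the usual linear-model variance inflation is 1/(1 − 0.22²) ≈ 1.05, so standard errors grow by about 2.5%; stronger clustering would raise this somewhat. The sample of 776 stays as it is.
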